### Bioavailability data analysis

Statistical analysis will be performed at IFR using R data analysis software [14]. Standard Linear Regression and ANOVA models will be used. For all models, regression diagnostics will be checked to determine if data transformations, outlier omissions or alternative non-parametric models are required. Results will be considered significant if P < 0.05 for all tests.

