### Randomisation to treatment

Randomisation was performed by an independent third party. Treatment codes were generated by ferritin stratification in blocks of 3 using a computer generated randomisation schedule. Three ranges of plasma ferritin were used for stratification; less than 15 ng/ml, 15.1–59.9 ng/ml and greater than 60 ng/ml. One in four women were allocated to the bioavailability arm by random sampling from those in the 4 mg and placebo groups of the intervention.

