#### Power calculation for the bioavailability

It was estimated that 15 subjects per group would be required to detect a 5% difference between the 4 mg and placebo intervention groups in iron incorporation into erythrocytes in response to intervention. This estimate was based on a mean bioavailabilty of 15% and a SD of 5% [9]with a power of 90% and a significance level of 0.05.

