### Initial Findings

#### Recruitment

Over a period of fifteen months, 256 women were screened for moderate riboflavin deficiency. From this initial screening, 145 were eligible for the intervention trial on the basis of an EGRAC>1.40. This represented 57% of our screened population. Of these 123 women agreed to take part in the main study (36 of these were randomly allocated to the bioavailability arm). In all, 4 women failed to complete the main study (none of whom, were in the bioavailability arm).

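### The bioavailability analysis lets model diagnostics on the outcome remove women as outliers while keeping P < 0.05, which raises the false-positive rate by an amount set by an unstated cut-off

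*Protocol article*

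**What the plan says.** The section Bioavailability data analysis sets the default: "Standard Linear Regression and ANOVA models will be used". It then adds that "regression diagnostics will be checked to determine if data transformations, outlier omissions or alternative non-parametric models are required", and closes with "Results will be considered significant if P < 0.05 for all tests". It gives no residual cut-off and no order for the three options. It does not say that diagnostics are read blind to arm, or that the analysis of all women is kept and reported.

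The comparison is small. Power calculation for the bioavailability states that "15 subjects per group would be required to detect a 5% difference between the 4 mg and placebo intervention groups", from a mean of 15% and an SD of 5%, "with a power of 90% and a significance level of 0.05". Under Initial Findings, Recruitment reports 123 women in the main study, of whom "36 of these were randomly allocated to the bioavailability arm", and none of the 36 dropped out. Randomisation to treatment says that they came by "random sampling from those in the 4 mg and placebo groups of the intervention". The split of the 36 between the two groups is not given.

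**The concern.** A residual diagnostic shows that a value is extreme under the fitted model. It does not show that the isotope dose, the sample or the assay went wrong, and the article asks for no such evidence before omission. Because all 36 women completed, any gap in the analysed data would be the analyst's choice and not missing data.

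If the two groups truly do not differ, removing the most extreme values makes the remaining data look less variable than the women really are. The standard error is then too small and the P value too low. The nominal 5% no longer describes the procedure. In a comparison of 36, one omitted woman is 1/36 = 2.8% of the data and two are 5.6%.

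Bioavailability is a stated objective with its own power calculation, although it is not listed under Primary Outcome Variables. What is at stake is the meaning of the P value for that objective, not the main haematological comparison.

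**Working it through.** **Inputs.** From the article: mean 15, SD 5, nominal level 0.05, 15 per group planned, 36 women in total. Assumed: two-sided tests, an equal split of the 36 (18 per group), one outcome value per woman, and data either normal or log-normal with this mean and SD.

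**The plan's own figure.** The only false-positive rate that the article implies is the nominal 5%. The t test on all women reproduces it under simulation (first row of the table). The 15 per group is used here only as a size. It does not follow from the simple two-group formula, since 2 × (1.960 + 1.282)² × 5²/5² = 21.0, that is 22 per group after rounding up. That is a separate question and nothing below depends on it.

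**Step 1: mechanism, large-sample normal case.** Let k be the cut-off in SDs, f the normal density at k, P = 2Φ(k) − 1 the share kept, d = 2kf, and V = P − d. Then:

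- residual variance after omission, relative to the truth: V/P
- actual variance of a group mean (× n/σ²): [V(1 + 2d) + d²]/P²
- variance that the t test uses (× n/σ²): V/P²
- actual level: 2[1 − Φ(1.96/r)], where r² is the actual variance over the variance used

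| k | f | P | d | V | V/P | actual | used | r | level |
|---|---|---|---|---|---|---|---|---|---|
| 3 | 0.0044 | 0.9973 | 0.0266 | 0.9707 | 0.973 | 1.029 | 0.976 | 1.027 | 5.6% |
| 2.5 | 0.0175 | 0.9876 | 0.0876 | 0.8999 | 0.911 | 1.092 | 0.923 | 1.088 | 7.2% |
| 2 | 0.0540 | 0.9545 | 0.2160 | 0.7385 | 0.774 | 1.212 | 0.811 | 1.223 | 10.9% |

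The test understates the variance at every cut-off, and more so as the cut-off tightens.

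**Step 2: simulation at the trial's sizes.** No treatment effect, t test at 0.05, externally studentised residuals, 4,000 replicates at n = 15 and 8,000 at n = 18. The simulation standard error at 5% is √(0.05 × 0.95/4,000) = 0.0034 and √(0.05 × 0.95/8,000) = 0.0024.

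| Rule | n = 15 normal | n = 15 log-normal | n = 18 normal | n = 18 log-normal |
|---|---|---|---|---|
| all women kept | 0.0435 | 0.0452 | 0.0499 | 0.0491 |
| omit beyond 3 | 0.0558 | 0.0630 | 0.0649 | 0.0632 |
| omit beyond 2.5 | 0.0765 | 0.0703 | 0.0845 | 0.0698 |
| omit beyond 2 | 0.1160 | 0.0915 | 0.1202 | 0.0951 |

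This gives about 6-7%, 7-8% and 9-12%, in line with step 1.

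**Step 3: which option drives it.** Results here also cover a more skewed log-normal (CV 0.8) and a heavy-tailed shape (t with 3 degrees of freedom).

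- Diagnostics choose only among raw scale, log scale and rank test (Shapiro-Wilk on residuals, then log, then Mann-Whitney): 0.046-0.056.
- The same kind of sequence with omission at 3 or 2.5 as one of the steps, ending in one test: 0.047-0.072.
- Smallest P value among t, log-t, Mann-Whitney and a t test with omission: 0.068-0.094 with the cut-off at 3, 0.084-0.102 at 2.5, 0.096-0.131 at 2.

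Omission is the driver. Diagnostic-led choice of scale or rank test barely moves the rate.

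**The case against.** The strongest reply is that the article says diagnostics decide whether such steps are required. It does not say that every large residual goes, or that the analyst may pick the best result. A cautious analyst who follows diagnostics to one final test ends at roughly 5-7%. A cut-off of 2 would remove someone from most clean datasets: treating residuals as independent and normal, 1 − 0.9545³⁰ = 75% with 30 women and 1 − 0.9545³⁶ = 81% with 36. That is hard to call omission only where needed. This stands. A reader might infer that the rule roughly doubles the false-positive rate. The article does not support that as a general statement, because it takes a liberal cut-off or picking the smallest P value across analyses that include omission, and the article states neither.

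Three further inferences also lack support:

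- **Right skew.** With mean 15 and SD 5, zero lies 3 SDs below the mean, so these figures alone do not suggest skew. The log-normal case above is an assumption.
- **Extreme values as genuine physiology of iron-depleted women.** The article neither says this nor rules out dosing or assay error.
- **Unnamed covariates as a fault.** A condensed article may leave model terms to a fuller plan.

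A fuller plan, not shown, may also fix a cut-off. That would settle the size of the inflation. It would not remove it, because omission beyond 3, 2.5 or 2 gave a rate above that of the all-women test in every case simulated.

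**Conclusion.** The point holds for outlier omission. It concerns something the article states, not detail left out: extreme residuals are a sufficient ground for removing randomised women, and the nominal threshold is kept. The direction is firm, by formula and by simulation. If omission is applied routinely, the size is about 6-7%, 7-8% or 9-12% at cut-offs of 3, 2.5 or 2, against about 5% with all women. If omission is only an occasional step in a diagnostic sequence, the excess can be negligible.

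These figures rest on two-sided tests, equal groups, the assumed distributions and a single value per woman. The design measures incorporation before and after intervention. A baseline-adjusted or change analysis would have the same mechanism, but its rates were not computed. Whether one or two omissions would change this trial's result cannot be known from the article.

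**What to change.** In Bioavailability data analysis:

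- Strike outlier omission from the options that diagnostics may trigger.
- Name one primary model, with its scale, for the 4 mg versus placebo contrast, and include every dosed woman. Adjusting for pre-intervention incorporation uses data already collected and can gain precision, by an amount that depends on its correlation with the outcome.
- Allow exclusion of a value only for a documented assay or dosing failure, decided blind to arm, and list each exclusion with its reason.
- Report rank-based, transformed or outlier-omitted results as sensitivity analyses beside the primary one.

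The Discussion says that the trial is complete and analysis is under way. The change should therefore be dated, with a statement of whether it came before or after anyone saw the bioavailability results by arm. If omissions have already been made, the result with all 36 women should be given first.

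The cost is a text change and slightly less freedom at the analysis stage. No new data or visits are needed.

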### Initial Findings

#### Recruitment

Over a period of fifteen months, 256 women were screened for moderate riboflavin deficiency. From this initial screening, 145 were eligible for the intervention trial on the basis of an EGRAC>1.40. This represented 57% of our screened population. Of these 123 women agreed to take part in the main study (36 of these were randomly allocated to the bioavailability arm). In all, 4 women failed to complete the main study (none of whom, were in the bioavailability arm).

#### Compliance

The mean compliance (± SD)of the volunteers as judged by the number of capsules returned was 96 ± 6%. (range 70–100)

#### Influence of recruitment to screening on riboflavin status

It was considered possible that the time taken between screening and starting the intervention trial might influence dietary change prior to starting the intervention. The median time that women had to wait before starting the intervention was 47 days (range 7–240). The main reason for delay was the coordination of the start of the study with the menstrual cycle. Other factors included the timing of vacations and the need to accommodate 4–6 visits over a period of 12–14 weeks depending on the arm of the study.

The mean EGRAC value for the entire screened population (n = 256) was 1.43 ± 0.18.

This is comparable with the EGRAC values reported in the most recent Diet and Nutrition Survey of adults in the UK for this age group (mean, 1.45 ± 0.19).

The mean (± SD) EGRAC value of these women recruited to the intervention study was 1.54 ± 0.14. The mean EGRAC value at baseline was significantly greater (1.59 ± 0.19) indicating a modest but significant deterioration in riboflavin status during the waiting period (*P *= 0.007)

## Discussion

Recruitment to the screening and intervention stages of this study was successfully completed within 16 months. The recruitment strategies that proved to be the most effective for this age group were the use of email and a web site, probably because these are familiar media and in use daily by this age group. There was also a good response from posters and leaflets but contact was generally then made via the web site and email. A short newspaper campaign was not successful in recruiting volunteers. Constant contact by email and the frequency of the visits contributed to a low drop out rate and helped maintain a high compliance rate. Financial reimbursement was also likely to have been a significant factor in obtaining a high recruitment rate and maintaining involvement in the study.

It was thought that volunteers enrolled into a nutrition study might modify their diet so as to increase their riboflavin intake during the period from screening until the start of the intervention study. However the volunteers in this study showed a deterioration in riboflavin status, evidenced by a small but significant increase in the mean EGRAC value.

The results of this study will provide valuable information about the effect of a riboflavin supplement on the haematological status of young women with marginal riboflavin status and help us to understand the functional significance of riboflavin deficiency. If an effect is demonstrated it will form the basis of a discussion to re-evaluate the EGRAC threshold for riboflavin deficiency.

The randomised controlled trial is now complete and the statistical analysis underway.
